#### Treatment outcomes

We define treatment success as a patient whose throat-swab SARS-CoV-2 real-time fluorescent reverse transcription polymerase chain reaction (RT-PCR) nucleic acid is positive at the beginning of the treatment but is negative at least twice consecutively after the treatment and remains negative.

### Participants

#### Inclusion criteria

Age ≥ 18 yearsPatients diagnosed with COVID-19 according to the criteria of the seventh edition of the Treatment Plan of China for new coronavirus pneumonia (URL: http://202.116.81.74/cache/4/03/www.nhc.gov.cn/5d9aa1423a8a577e1cc197a0d3c434d8/ce3e6945832a438eaae415350a8ce964.pdf):
① Epidemiological history:
Within 14 days before the onset of illness, a history of travel or residence in Wuhan and surrounding areas, or other communities with reported casesWithin 14 days before the onset of illness, exposure to a person with COVID-19 infection (positive nucleic-acid test)Exposure to patients with fever or respiratory symptoms from Wuhan and surrounding areas, or communities with case reports within 14 days before illness onsetAggregated disease: two or more cases of fever or respiratory symptoms occurring in a small area, such as home, office, school class, etc., within 2 weeks② Clinical manifestations:
Fever or respiratory-tract symptoms: cough, nasal stuffiness, nasal discharge, etc.Normal or decreased white-blood-cell counts in the early stages of disease; normal or decreased lymphocyte countsMultiple, small, patchy shadows and interstitial changes in the early stages of chest imaging, which are evident in the extrapulmonary zones, and which develop multiple “ground-glass” infiltrations and infiltrates throughout both lungs. In severe cases, pulmonary consolidation may occur, but the formation of pleural effusion is rare③ Confirmed conditions: fulfillment of any one of the epidemiological history items and any two of the clinical manifestation items or three clinical manifestation items if no epidemiological history is available, in addition to meeting one of the following etiological or serological criteria:
Real-time fluorescent RT-PCR detects novel coronavirus nucleic acidThe gene-sequencing results of patients’ specimens (blood, stool, etc.) are highly homologous to those of known novel coronavirusesSerum SARS-CoV-2-specific antibodies IgM and IgG are positive, serum SARS-CoV-2-specific IgG antibodies change from negative to positive or the quantity of IgG in the recovery phase is at least four times higher than in the acute phase (3–5 days after illness onset)Mild or general patients:
Mild: mild clinical symptoms (only manifested as low-grade fever, minimal fatigue, etc.), and no pneumonic manifestations on imagingGeneral: with fever, dry cough and other respiratory-tract symptoms, visible pneumonic imaging)Those who have not used antiviral drugs

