### Definitions

#### The clinical recovery time and adverse events

We define the clinical recovery time as the time (in hours, no more than 28 days) from the start of study drug intervention to normalization of body temperature, respiratory symptoms (cough, nasal stuffiness, nasal discharge, etc.), respiratory frequency, and blood-oxygen saturation. Specifically, also meeting the following criteria at the same time:
① No fever: axillary body temperature ≤ 37.2 °C② Relief of respiratory symptoms (72 consecutive hours)③ Respiration rate ≤ 24/min (resting state)④ Fingertip blood oxygen > 94%

Adverse events (AEs) refer to adverse medical events that occur after a patient or clinical trial participant receives a drug, but they are not necessarily causally related to treatment.

Serious adverse events (SAEs) refer to events that require hospitalization, prolonged hospital stay, disability, affect working ability, are life-threatening or fatal, cause congenital malformation and other events that occur during the clinical trial.

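### Eligibility does not require any recovery criterion to be unmet at day 0, so patients whose symptoms have already resolved can be randomised and counted as recoveries that carry no treatment information

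*Protocol article*

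**What the plan says.** **Endpoint.** Under the definition of clinical recovery time, the clock runs "from the start of study drug intervention to normalization of body temperature, respiratory symptoms", respiratory rate and oxygen saturation, in hours and for at most 28 days. Four conditions must hold together: "No fever: axillary body temperature ≤ 37.2 °C"; "Relief of respiratory symptoms (72 consecutive hours"; "Respiration rate ≤ 24/min (resting state"; and fingertip oxygen saturation above 94%. The text does not say whether the 72-hour condition dates the event at the start or the end of the 72 hours.

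**Entry.** The Inclusion criteria ask for age 18 or over, a confirmed diagnosis, mild or general class, and no previous antiviral drugs. The clinical part of the diagnosis is "any one of the epidemiological history items and any two of the clinical manifestation items", or all three clinical items without an epidemiological history. The three items are fever or respiratory symptoms, blood counts early in the disease, and imaging changes. One laboratory route to confirmation is that "the quantity of IgG in the recovery phase is at least four times higher than in the acute phase". Mild disease is described as "only manifested as low-grade fever, minimal fatigue, etc", with no pneumonia on imaging. General disease has fever, dry cough and other respiratory symptoms, with visible pneumonia. The Exclusion criteria concern allergy, comorbidity and pregnancy only.

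**Size.** The Sample size section assumes medians of 8 days (control) and 4 days (experimental), a hazard ratio of 2.0, two-sided α of 0.05, 112 patients, and a final analysis after 78 recovery events. The 85% is worded as a confidence interval and is read here as power.

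**The concern.** A time-to-recovery comparison informs about treatment only through patients who still have something to recover from when the clock starts. Entry is defined by how the illness was diagnosed and classed, not by the patient's state at day 0. A patient who had fever and cough, is correctly classed as mild or general, and has since become symptom-free meets every entry criterion. If the four recovery criteria hold at the first dose and continue to hold, that patient is an event at the same time in either arm.

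This has two consequences. First, the log-rank and Cox analyses mix informative events with events unrelated to treatment, which pulls the hazard ratio toward 1. Second, the final analysis is triggered by a count of recoveries, so these patients use up part of the 78 events on which the power rests.

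The protocol does set a baseline condition for a secondary outcome: treatment success requires a positive swab at the start of treatment. The primary outcome has no counterpart.

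**Working it through.** **1. Who can enter**

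| Patient | Reaches the clinical items? | Fits a class? |
|---|---|---|
| Never symptomatic; blood count and imaging changes | Yes (two items), with an epidemiological history | No: visible pneumonia means general, which is described with fever and dry cough |
| Mild, fatigue only, no imaging signs | No: only the blood count is met | Class fits, diagnosis fails |
| Fever or cough earlier, resolved before day 0 | Yes | Yes: nothing ties the class to day 0 |

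The third row is the gap. No limit on time since onset closes it.

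**2. The plan's own event count**

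Inputs from the Sample size section: HR 2.0, two-sided α 0.05, power 85%, 1:1 allocation.

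- Schoenfeld: 4(1.960 + 1.036)² / (ln 2)² = 74.7, so 75 events.
- Freedman: (1.960 + 1.036)² × (3/1)² = 80.8, so 81 events.
- Lakatos calculation with medians of 8 and 4 days: 77 to 80 events, depending on how follow-up and drop-out are read.

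The stated 78 reproduces. Power at 78 events is Φ(√78 × ln 2 / 2 − 1.960) = 86.5% by Schoenfeld, and Φ(√78 / 3 − 1.960) = 83.7% by Freedman.

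**3. Simple count of informative events**

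Let f be the share already recovered at day 0. The documents do not give f; 0 to 30% is an assumption. With all 112 enrolled, informative events among the 78 number 78 − 112f.

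| f | Informative events | Schoenfeld power |
|---|---|---|
| 0 | 78 | 86.5% |
| 10% | 66.8 | 80.9% |
| 20% | 55.6 | 73.4% |
| 30% | 44.4 | 63.7% |

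This is only a guide: it credits the informative events in full and ignores the noise that the uninformative ones add to the test.

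**4. Simulation of the stated analysis**

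Setting: 56 per arm, uniform entry over 90 days, exponential recovery with medians 8 and 4 days in patients not yet recovered, 28-day cap, 5% drop-out in total, analysis at the 78th event, log-rank test, and Cox model with Efron ties; 1,500 trials per cell. A second, separate simulation at 78 events gives the second power figure in each cell. At f = 0 the dating is irrelevant, so the spread there is simulation error.

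| f | Power, dated 0 h | HR, 0 h | Power, dated 72 h | HR, 72 h |
|---|---|---|---|---|
| 0 | 86 / 84% | 2.03 | 86 / 82% | 2.05 |
| 10% | 76 / 78% | 1.86 | 79 / 78% | 1.91 |
| 20% | 65 / 65% | 1.72 | 71 / 72% | 1.79 |
| 30% | 53 / 55% | 1.57 | 63 / 68% | 1.68 |

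Leaving these patients out by their day-0 status gives about 82–86%.

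**5. Are 78 at-risk events within reach of 112 patients?**

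The chance of recovery by day 28, averaged over the arms, is [(1 − 2^(−28/8)) + (1 − 2^(−7))] / 2 = 0.952. Expected at-risk events are 112 × 0.95 × 0.952 × (1 − f), which is 101, 91, 81 and 71 for f = 0, 10, 20 and 30%. So 78 can be reached up to about f = 20%. At 30% the trial ends near 71 events, with 83% power.

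**The case against.** **Stronger readings that the text does not support.** A reader might infer from the two-of-three rule that a patient who never had fever or cough qualifies on blood count and imaging, or that a mild patient with fatigue alone does. The class definitions block the first, and the two-item requirement blocks the second. The recovery-phase antibody route shows only that confirmation can come late. It waives neither the clinical items nor the class.

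**The wording of the endpoint.** The outcome is "normalization of body temperature, respiratory symptoms (cough, nasal stuffiness, nasal discharge, etc.), respiratory frequency, and blood-oxygen saturation", and one could argue that normalization presupposes an abnormal start. The listed criteria do not say so. If that reading were intended, a patient already normal at day 0 would have no defined outcome, so a rule is still needed. Nor is an event at time zero settled: dated at the end of the 72 hours it falls at 72 h, and the loss is smaller.

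**The size.** The share f has no basis in the documents. The Sample size section gives the medians of 8 and 4 days for the patients of each group, without separating those already recovered. If they describe everyone enrolled, part of the dilution is already in the plan. A reader might also start from about 95% power, which comes from following all 112 patients to 28 days. There, power with events at 0 h is 87, 80 and 71% for f = 10, 20 and 30%. But the plan analyses at 78 events, so that is not the relevant baseline.

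**What the full protocol may hold.** An article may leave the handling of such patients to the full protocol or the analysis plan. That answers part of the point, but not the entry criteria, which are set out here item by item and contain no day-0 condition.

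What stands is the patient whose symptoms resolved before the first dose.

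**Conclusion.** The gap is real, though narrow: entry is not tied to the patient's state at day 0, and patients already meeting all four recovery criteria can be randomised and counted toward the 78 events. The direction is certain if such patients are enrolled and counted: the hazard ratio moves toward 1 and power at 78 events falls.

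The size is conditional. Against about 84–86% with no such patients, an assumed 10, 20 or 30% gives power of roughly 76–78, 65 or 53–55% if events are dated at 0 h, and 78–79, 71–72 or 63–68% if dated at 72 h. The hazard ratio falls from about 2.0 to about 1.9, 1.7–1.8 or 1.6–1.7 (0 h). These figures assume exponential times, 5% drop-out in total, and medians of 8 and 4 days in the patients not yet recovered. If the planned medians already include early recoveries, the loss is smaller. If few such patients present, it is negligible.

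**What to change.** 1. **Eligibility, for patients still to be enrolled** (Trial status says recruitment is ongoing): require at least one of the four recovery criteria to be unmet on values recorded before randomisation.
2. **Analysis, for the whole trial:** before any analysis, pre-specify a log-rank and Cox comparison restricted by that same pre-randomisation condition, reported alongside the analysis of all randomised patients. Because the set depends only on values recorded before allocation, the randomised comparison is preserved.
3. **Event count:** let only recoveries in patients at risk at day 0 count toward 78. Add a stopping point for the case that 78 is out of reach, such as completion of 28-day follow-up in the last patient.
4. **Dating:** state whether the 72-hour recovery is dated at its start or its end.

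The cost is slightly slower enrolment and a somewhat smaller analysed set, with no extra visits. The shortfall depends on drop-out. The stated 112 reproduces (110–111) only if the 5% is a daily rate, with about 0.70 events per patient. Then 112 × 0.70 = 78 events are expected in all, and restriction leaves about 78 × (1 − f): 70, 62 and 55 for f = 10, 20 and 30%. With 5% in total, there is the room shown in step 5 of the working. The drop-out unit should be settled at the same time.

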#### Exclusion criteria

Any of the following factors will lead to exclusion:
Patients with a history of allergy to chloroquine phosphate, lopinavir, or ritonavirPatients with hematological diseasesPatients with end-stage liver or kidney diseasesPatients with arrhythmia and/or chronic heart diseasePatients known to have retinal disease or hearing lossPatients known to have mental illnessPatients who must use digitalis because of an original underlying diseasePancreatitisHemophiliaFavismFemale patients during pregnancy

### Randomization

Grouping is carried out using a centrally stratified, randomized block method. Before the trial, a statistical expert will use SAS software to set the number of centers at four, the block size will be four, the number of blocks will be 28, using a 1: 1 ratio between the experimental group and the control group, will generate 112 random numbers and corresponding grouping information. According to the haphazard allocation table used in advance, the statistical expert gives random numbers (1–112) in ascending order. Each random number and grouping information correspond to an envelope. The envelope is sealed and given to the researchers responsible for screening. Qualified subjects are selected, and the envelopes are received in the order of enrollment. After the envelopes are opened, the random-number and grouping information is removed, so that the subjects will be randomly assigned to the experimental group or the control group, and the corresponding treatment and observations performed. Each subject’s random number is unique and remains the same throughout the trial.

### Sample size

The hypothesis of this study is that the use of chloroquine phosphate instead of lopinavir/ritonavir will increase the rate of throat-swab SARS-CoV-2 nucleic-acid negative conversion.

The main therapeutic index of this study is the clinical recovery time (after no more than 28 days), which is from the beginning of the study drug intervention treatment to the normalization of body temperature, respiratory symptoms, respiratory rate, and blood-oxygen saturation. In the later analysis, the log-rank method is used to compare the differences in clinical recovery time between the two groups of patients. The sample size of this study is calculated based on the log-rank method by using the log-rank test (Lakatos) (median survival time) module in the PASS 11.0 statistical software (see Additional file: Sample size report” for details).

Based on clinical experience [4, 18], the median clinical recovery time of the patients in the control group is expected to be 8 days, and the median clinical recovery time of patients in the experimental group can be shortened to 4 days (corresponding hazard ratio (HR) = 2.0) 112 patients (56 in each group) will be required to detect this difference with a significant level of *α* = 0.05 (both sides) with 85% confidence interval.

The trial is planned to be enrolled for 90 days, followed up for 28 days, and a final analysis is performed after 78 clinical recovery events occur. It is estimated that the drop-out rate of the experimental group and the control group is 5%.

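### The 112 patients, 78 events and 5% drop-out do not fit together if the 5% is total loss, and 78 events is an unreliable trigger for the final analysis

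*Protocol article*

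**What the plan says.** All the figures stand in the Sample size section of the protocol article. The control arm's planning value is that "the median clinical recovery time of the patients in the control group is expected to be 8 days"; chloroquine is expected to halve this to 4 days, a hazard ratio of 2.0. The requirement is "112 patients (56 in each group) will be required to detect this difference", at a level given as "0.05 (both sides) with 85% confidence interval". On timing: "The trial is planned to be enrolled for 90 days, followed up for 28 days", and then "a final analysis is performed after 78 clinical recovery events occur". On losses: "It is estimated that the drop-out rate of the experimental group and the control group is 5" (per cent, with no period attached). The method is the Lakatos log-rank module of PASS 11.0, with details referred to an additional sample-size report that is not shown.

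Elsewhere, the Randomization section prepares 28 blocks of four, that is 112 envelopes. The primary outcome is recovery time up to 28 days, and the Statistical analysis sections report it as a proportion per arm before the log-rank test. The rate of treatment success is compared after therapy and follow-up are complete.

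**The concern.** A 5% drop-out rate without a unit is naturally read as 5% of patients lost over the study. On that reading, almost everyone recovers within 28 days under the planned medians, so 112 patients should produce far more than 78 events. Either the sample size or the event count then does not belong with the stated losses.

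The event count is also made the occasion for the final analysis. If 78 recoveries accumulate while patients are still being enrolled, the plan contains two incompatible end points for the trial: 78 events, or 112 patients each followed for 28 days. The 28-day proportions and the treatment-success rates need the second. In an open-label trial the time at which the database is declared final should not be open to interpretation.

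**Working it through.** **Inputs from the article:** medians 8 and 4 days, 1:1 allocation, two-sided 5%, 85% read as power, 90 days of accrual, 28 days of follow-up, N = 112, 78 events, 5% drop-out. **Assumptions not in the article:** exponential recovery times and uniform accrual. Hazards are ln 2/8 = 0.0866 and ln 2/4 = 0.1733 per day.

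**1. Is 78 a sensible event count?** (1.960 + 1.036)² = 8.98.
- Schoenfeld: 4 × 8.98/(ln 2)² = 74.7 events.
- Freedman: 8.98 × (3/1)² = 80.8 events.
- Power at 78 events: Φ(√78 × ln 2/2 − 1.960) = 86% (Schoenfeld); Φ(√78/3 − 1.960) = 84% (Freedman).

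So 78 events match 85% power.

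**2. Reproducing 112 and 78.** Take 5% as a daily loss: loss hazard −ln 0.95 = 0.0513 per day. With 90 days of accrual and 28 days of further follow-up, the event probabilities are 0.627 (control) and 0.772 (chloroquine). Then 56 × 0.627 + 56 × 0.772 = 78.3 events. The Lakatos calculation gives N = 110.4, hence 56 per arm, with about 85.5% power at 112. Both printed figures are recovered.

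With no loss, or with 5% per week, per 10, 28, 30 or 118 days, N is 81–86 (85–90 after dividing by 0.95). None gives 112.

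**3. What 5% per day implies.** Patients lost before recovery within 28 days, loss hazard/(total hazard) × [1 − exp(−28 × total hazard)]:
- control: 0.0513/0.1379 × 0.979 = 36%
- chloroquine: 0.0513/0.2246 × 0.998 = 23%

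**4. What 5% in total implies.** Recovery by day 28 without loss is 1 − 2^(−28/8) = 0.912 and 1 − 2^(−28/4) = 0.992, mean 0.952.
- No loss: 112 × 0.952 = 106.6 events.
- 5% lost evenly over 28 days: probabilities 0.897 and 0.982, mean 0.940, so 105.2 events.
- 5% lost at day 0: 106.6 × 0.95 = 101.3 events.
- Patients needed for 85% power (Lakatos): 82–83, or 86–87 after dividing by 0.95.
- Power with all 112 followed: 92% (Freedman, 101.3 events) to 94% (Schoenfeld, 105.2 events; Lakatos 93.7%).

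**5. When does the 78th event fall with 5% in total?** Accrual is 112/90 = 1.244 per day. For t between 28 and 90 days, expected events are 1.244 × [A + (t − 28) × p], where p is the 28-day event probability and A the integral of the event probability from 0 to 28 days.
- Planned effect, no loss: A = 19.88, p = 0.952. 78/1.244 = 62.68, so t = 28 + (62.68 − 19.88)/0.952 = day 73.
- Planned effect, 5% over 28 days: A = 19.69, p = 0.940, so t = day 74.
- No effect (both medians 8 days): A = 17.48, p = 0.912 without loss gives day 78; A = 17.28, p = 0.897 with 5% loss gives day 79.

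At day 74 about 92 patients are enrolled (74 × 1.244) and about 20 are not. About 35 of those enrolled (28 × 1.244) entered within the last 28 days and cannot yet have reached D28.

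**6. And with 5% per day?** With the 28-day cap the probabilities are 0.615 and 0.770, so 77.6 events are expected from all 112 patients. Simulation reaches 78 in about 52% of trials.

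**The case against.** The strongest reply is that 112 and 78 do belong together: one coherent input reproduces both, and the unseen sample-size report may state that unit. This stands as far as it goes. The daily rate is an inference, though a strong one given that every other unit tried fails. If the report confirmed it, the article would still print a bare 5% for an assumption under which a third of controls are lost.

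Second, the early trigger and the reproduction of 112/78 rest on different readings of the 5%, and cannot be charged to the plan at once. That is right. Under 5% per day the difficulty is the reverse one: 78 is roughly all the events the trial expects, and may not be reached.

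Third, the timing sentence can be read in sequence: enrol, follow up, then analyse, with 78 as the required count. That reading is possible and removes the early analysis. It then leaves unexplained why 78 is the condition when about 101–105 events are expected under 5% total loss.

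Fourth, day 73–78 is model-based. Recovery requires 72 consecutive hours of symptom relief; if it is recorded three days later, the date under the planned effect moves to about day 76 with 95 enrolled, and with back-loaded accrual as well to about day 87 with 105 enrolled. The direction holds in these variants; the number of outstanding patients does not.

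**Conclusion.** The inconsistency is real. If 5% is total drop-out, 112 is about 25–30 patients more than 85% power requires, and the expected events are about 101–105, not 78. As a trigger, 78 events works under neither reading: it comes before enrolment is complete if losses are 5% in total, and is about an even chance if they are 5% per day. The size rests on exponential recovery at the planned medians and, for the calendar date, on uniform accrual and prompt recording of recovery.

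Three stronger readings are not supported:
- A reader might infer that the trial is underpowered or that 85% is not its power. At 78 events the power is 84–86%, and with full follow-up of 112 it is higher.
- A reader might infer that patients would be randomised after the result is known. The article does not say what happens to enrolment at event 78, nor that results would be released.
- A reader might say that a daily 5% loses 76% of patients by day 28 (1 − 0.95^28). That holds only if nobody recovers; under the planned medians the losses before recovery are 36% and 23%.

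The phrase "with 85% confidence interval" is a mislabel: the figure functions as power, as the reproduction confirms.

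**What to change.** Perform the final analysis once all 112 randomised patients have completed D28, in place of the 78-event condition. State the time unit of the drop-out rate and rerun the Lakatos calculation with 5% as the total. Restate about 101–105 expected events and about 92–94% power for a hazard ratio of 2.0 at N = 112, and describe the 85% as power, the original planning target.

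The cost is a change of wording and one rerun of the sample-size module. No extra patients are needed. The analysis falls at about day 118, which 90 + 28 days already implies, and so later than a literal 78-event trigger would give.
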